### Blinding

Because of acupuncture’s nature, blinding the physician involved in the treatment application is impossible. Each hospital will designate several operating researchers who are dermatologists trained to perform EA therapy and obtain relevant operational qualifications. Therefore, operating researchers will not participate in the statistical analysis; the treatment plan and grouping will be known only by statistical analysts. To ensure blinding, we will choose the Park Sham Device (PSD) as a placebo control in a single-blind clinical trial, use a way of not energizing the EA device, and use black eye masks to shield the participants’ eyes. The treatment device will also be the same size and material, and the treatment method will maintain a consistent frequency and intensity.

In the case of serious adverse events, the principal investigators at each participating center will decide whether allocation concealment needs to be broken. If allocation concealment is broken before the end of the trial, the data will be censored from analysis and the patients will be considered to have dropped out of the trial.

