**Figure 4 fig4:**
[figure not shown]
Location of verum acupoints and sham acupoints.

Achieving qi (a combination of sensations, including soreness, numbness, distention, heaviness, and other sensations) is considered an important part of obtaining the efficacy of acupuncture. Four pairs of electrodes are used: two each on bilateral *Quchi* (LI4) and *Hegu* (LI11) and two each on bilateral *Xuehai* (SP10) and *San Yinjiao* (SP6); they are all ipsilateral to one another. The duration of the EA stimulation is 30 min, with the current intensity of 1–5 mA with a continuous wave of 20 Hz (with the skin around the acupoints shivering mildly without pain). For 2 weeks straight, the participants will have three therapy sessions each week for a total of six sessions.

Participants in the SEA group will receive SEA with PSD but without energizing the electropuncture device. Procedures, electrode placements, and other treatment settings will be the same as those in the EA group but with no electricity output.

Participants in the SAC group will receive sham acupuncture with PSD and PSN at sham acupoints (non-meridian and non-acupuncture points). The sham acupoints selected for this study, based on reports from other scholars, are as follows: (33) The sham *Hegu* (LI11) is located at the dorsum of the hand, between the first and second metacarpals, 1 cun [≈10 mm] next to the midpoint of the radial side of the second metacarpal. The sham *Quchi* (LI4) point is at the midpoint between the locations of verum *Quchi* and *Chize*; the sham *Xuehai* (SP10) point is 1 cun [≈10 mm] lateral to the verum *Xuehai*; the sham *San Yinjiao* (SP6) point is at 3 cun [≈10 mm] above the tip of the lateral ankle, between the stomach and bile meridians.

Procedures, electrode placements, and other treatment settings will be the same as those in the EA group, but with no skin penetration, electricity output, or needle manipulation to achieve qi.

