We propose a prospective, multicenter, randomized controlled study of AE. The multicenter model considers the effect of environmental factors and individual participant characteristics on trial results, providing more reliable clinical evidence. We designed three arms to compare the effectiveness of EA and acupuncture and to establish the genuineness and credibility of the acupoints while eliminating any potential placebo effect. The objective VAS score was adopted as the primary outcome measure, and the EASI and DLQI scores as the secondary outcome measures, which should improve the reliability of the results. In addition, physical examination, personal life history, safety evaluation, patient satisfaction, and other outcome measures have been added. Keeping participants closer to the clinic helps track the disease progression in a clinical setting.

The study design has limitations. First, the sample size is only 132 participants. Second, the study duration is limited to 3 weeks without a follow-up period. Observing the long-term effects of the EA anti-itch technique on the progression of AE with a limited sample size and follow-up period will be challenging. However, we will use unique experimental designs and outcome measures to improve the accuracy and sensitivity of this study to mitigate these limitations.

In summary, this multicenter, randomized, sham electroacupuncture–controlled study will assess the effect on pruritus, clinical efficacy, and safety of the acupuncture antipruritic technique in AE. We will also establish a multicenter clinical registration platform and evaluate clinical evidence by assessing the treatment’s therapeutic benefits (clinical effectiveness with no adverse side effects). The findings will aid decision-making for managing and treating AE and offer crucial data that could be integrated into future clinical recommendations.

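### The listed blinding measures do not mask the felt difference between powered EA and unpowered SEA, and the itch VAS that is exposed to it is called objective

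*Protocol article*

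**What the plan says.** The article describes a single-blind trial. On operators, the Blinding section says: "Because of acupuncture’s nature, blinding the physician involved in the treatment application is impossible". For participants it names the Park sham device and says the trial will "use a way of not energizing the EA device, and use black eye masks to shield the participants’ eyes". It then adds: "The treatment device will also be the same size and material, and the treatment method will maintain a consistent frequency and intensity".

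The Intervention section sets EA at 1–5 mA and 20 Hz for 30 minutes, "with the skin around the acupoints shivering mildly without pain", in six sessions over two weeks. SEA has the same procedures, electrode placements and settings; these "will be the same as those in the EA group but with no electricity output". SAC uses the Park sham needle at sham points, with no penetration, no current and no manipulation to obtain qi.

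The section on the Park device gives its purpose as keeping participants from noticing whether the needle is real or sham. The Intervention section says that all three groups have the device.

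The primary outcome is improvement in VAS after two weeks, scored for pruritus. The Discussion says: "The objective VAS score was adopted as the primary outcome measure". It also says that the three-arm design removes any possible placebo effect.

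**The concern.** EA versus SEA is the contrast that isolates the electrical current. It is also the smallest of the three differences implied by the sample-size means: 4.7, against 5.5 for SEA–SAC and 10.2 for EA–SAC. Operators know the allocation, so participant blinding is the main protection for a self-rated outcome.

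If participants can feel whether current is flowing, their expectation can move their itch rating, and this cannot be separated from an effect of the current. The article presents that risk as dealt with: it says the treatments are matched in intensity, it calls the VAS objective, and it says placebo effects are excluded. For this contrast, the measures it describes support none of these three statements.

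**Working it through.** **1. Each measure set against the felt difference between EA and SEA**

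| Measure in the Blinding section | What it hides | Effect on EA vs SEA |
|---|---|---|
| Park sham device | Real versus sham needle | None: both arms have the device, and only SAC is described with the sham needle |
| Eye mask | Sight of the stimulator and needles | Does not hide a felt current or muscle response |
| Same size and material | Appearance | Does not affect sensation |
| Stimulator not energised | Nothing: it is the treatment difference itself | Creates the contrast to be masked |

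**2. The matching statement.** The Blinding section says "the treatment method will maintain a consistent frequency and intensity". The Intervention section gives EA a "current intensity of 1–5 mA with a continuous wave of 20 Hz (with the skin around the acupoints shivering mildly without pain" and SEA zero output. *Frequency* can be read as sessions per week, which is three in every arm, so that part can stand. *Intensity*, compared between arms, cannot be reconciled with 1–5 mA against none.

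**3. The outcome.** Itch on a VAS is the participant's own rating, so belief about treatment can enter it directly.

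**4. Which SD the plan implies.** The Sample size section gives n = 2[σ(Z(1−α/(2τ)) + Z(1−β))/(μA − μB)]², with α = 0.05 and power 0.80, but states neither σ nor τ. So n = 35 cannot be reproduced directly. The dropout step can be: 35/0.8 = 43.75, rounded up to 44, and 3 × 44 = 132. Solving for σ at n = 35:

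σ = √(35/2) × difference / (Z(1−α/(2τ)) + Z(0.80))

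- EA–SEA, difference 40.4 − 35.7 = 4.7: σ = 7.0 (τ = 1), 6.4 (τ = 2), 6.1 (τ = 3).
- EA–SAC, difference 45.9 − 35.7 = 10.2: σ = 15.2, 13.8, 13.2.

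**5. Illustration of the consequence.** The bias values are assumptions; the documents give none. Suppose SEA participants who recognise that there is no current rate their itch 5 points worse. The spurious difference is then the share who recognise it × 5:

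- 25%: 1.25 points, 27% of 4.7
- 50%: 2.5 points, 53% of 4.7
- 75%: 3.75 points, 80% of 4.7

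These figures scale in proportion to the assumed 5 points.

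The chance of a significant EA–SEA result with no true effect, by normal approximation at two-sided 0.05 with n = 35 per arm, is

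P = 1 − Φ(1.96 − b/SE) + Φ(−1.96 − b/SE), with SE = SD × √(2/35).

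For b = 2.5:

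- SD 6.1: SE = 1.458, b/SE = 1.714, P = 0.403
- SD 10: SE = 2.390, b/SE = 1.046, P = 0.182
- SD 20: SE = 4.781, b/SE = 0.523, P = 0.082

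Other values of b, at the SDs implied in step 4:

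| Bias (points) | SD 6.1 | SD 7.0 | SD 13.2 | SD 15.2 |
|---|---|---|---|---|
| 1 | 0.11 | 0.09 | 0.06 | 0.06 |
| 2 | 0.28 | 0.22 | 0.10 | 0.09 |
| 4.7 | 0.90 | 0.80 | 0.32 | 0.25 |

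The nominal rate is 0.05 throughout.

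**The case against.** **A reader might infer that the blind is bound to fail.** The documents do not show this. They hold no data on allocation guesses, and what participants are told to expect is not visible. SEA appears to keep real needling and the attempt to obtain qi, since only SAC is said to lack them. Soreness, numbness or distention could be taken for stimulation. This objection stands: the text supports only that the measures described do not mask the difference.

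**A reader might infer that the current is raised until the skin visibly twitches.** The article mentions mild shivering without pain, in a parenthesis. It does not describe stepwise adjustment to a visible endpoint.

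**A reader might infer that the trial will not record what participants believed.** This is a condensed article and its assessment schedule (Figure 2) is not shown. A guess question may sit in the full protocol, so its absence here is no finding.

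**The matching sentence may only be loose wording.** The sentence before it openly says that the device is not energised, and *consistent* could mean across sessions or sites. That is possible. But the paragraph is about securing the blind, where a comparison between arms is the natural reading, so the wording still needs correcting.

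**Other outcomes are less exposed.** Serum IgE is not self-reported, and EASI is also collected. They could support or weaken an EA–SEA finding, so expectancy would weaken the inference and not void it. Neither is the primary outcome, and neither is a rating of itch.

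**The 40% figure pairs assumptions unfavourably.** SD 6.1 follows from τ = 3, where the matching alpha is 0.05/3; the rate at that alpha is about 25%. With τ = 1 (SD 7.0, alpha 0.05) it is about 32%. The Statistical analysis section does set p < 0.05, so 40% is a legitimate value, but it lies towards the upper end for a 2.5-point bias. If n = 35 came from the EA–SAC pair, the SD is 13 to 15 and the inflation is much smaller.

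**Conclusion.** The point holds as a mismatch between what the article states and what the design provides. The listed measures do not mask the felt difference between EA and SEA. The statement of consistent intensity conflicts with the Intervention section. The VAS is self-reported, not objective. For EA versus SEA, the claim that placebo effects are excluded is therefore unsupported.

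The size of any bias is unknown. For an assumed 2.5-point bias, the false-positive rate is between about 8% (SD 20) and 40% (SD 6.1) instead of 5%; a smaller bias gives less. The conclusion rests on the text, not on any one of these values. An unpowered sham is a defensible comparator; the assurance attached to it is not. The change should be made, because it alters what a positive EA–SEA result can be said to show.

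**What to change.** 1. Reconcile the Blinding and Intervention sections: state that electrical output differs between the arms by design, and that what is kept the same is the session schedule and the procedures. No stimulation setting changes.
2. Use the same scripted statement in all arms, at consent and before sessions, that stimulation may or may not be felt.
3. Unless the full protocol already does so, ask each participant one allocation-guess question after the first session and at week 2. Report it by arm, for example with the Bang index, beside the VAS result.
4. In the Discussion, replace *objective* with *self-reported* and limit the placebo claim. Prespecify that an EA–SEA difference will be read as possibly including expectancy if guesses differ between the arms.

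The cost is a short script, one question asked twice at contacts that already exist, and wording changes. The article says that enrolment had not begun at the version it describes. The downside is that the trial may have to report that the EA–SEA blind failed.

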### Eligibility criteria

Inclusion criteria:

To be eligible for recruitment, the patient must:Be diagnosed with AE for a duration longer than 2 months.Be aged 18–65 years (male or female).Have body surface area (BSA) scores <10%.Provide consent to participate in clinical trial observation and cooperation with scheduled follow-ups.Sign and date the informed consent form.

Exclusion criteria:

Patients who meet any of the following criteria will be excluded:Have been systematically treated with drugs, such as hormones or immunosuppressants, within 2 weeks.Do not tolerate acupuncture.Signs of serious secondary infections, including localized skin infections and infections of other organs.Pregnancy, lactation, or planning to become pregnant during the trial.Diabetes or a combination of severe heart, liver, or kidney diseases.Received other investigational drugs or participated in other clinical trials within 3 months.BSA scores ≥10%.Unable to cooperate with the study for any reason, such as impaired language comprehension or inability to visit the study center.Generalized eczema with lesions spreading over the body is unsuitable for acupuncture.Acute flare-ups.

Drop-out exclusion criteria:

Patients who meet any of the following criteria will be a dropout case; if the time is past the mid-point of participation in the overall study, the data should be included in the efficacy statistics:Experienced unexpected events during treatment and are unfit to continue with the trial.Develop other illnesses during the course of the trial that affect judgments of efficacy and safety.Lack of compliance or voluntarily accepting other treatments during the course.Information is incomplete and affects judgments of efficacy and safety.Changed their contact details, resulting in loss of contact.

Exit/termination criteria:Patients who have experienced severe adverse reactions during treatment and whose treating physician assessed that the trial is no longer appropriate.Patients’ unsolicited requests to withdraw from the trial should be recorded, and the reasons noted.

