### Statistical analysis

Professional statisticians developed a statistical analysis plan upon consultation with the primary investigators. The data will be stored in the Data Management Center of Jiangsu Famous Medical Technology Co. Ltd. and processed by in-house statisticians blinded to group allocation.

All statistical analyses are performed using R [version 4.1.3; R Core Team (2022). R: A language and environment for statistical computing. R Foundation for Statistical Computing, Vienna, Austria^2^]. Statistical significance is set at value of *p* < 0.05. The intention-to-treat analysis population, consisting of all participants who pass the randomization stage, will be the primary population for demographic and other baseline characteristics, compliance, efficacy analysis, and safety analysis.

The analytical methods will be combined with descriptive and comparative analyses. Qualitative data will be described by frequency tables, percentages, or composition ratios; comparative analyses will be conducted using the chi-squared test, Fisher’s exact test, Wilcoxon rank-sum test, Cochran–Mantel–Haenszel test, and weighted least-squares covariance. Quantitative data will be described as the mean, standard deviation, median, quartile, minimum, and maximum. The *t*-test will be used for comparative analysis of data with normal distributions and with Satterthwaite correction if the variance is uneven. Quantitative data exhibiting a non-normal distribution on the Wilcoxon rank-sum test will be analyzed using the Wilcoxon signed-rank sum test and covariance generalized linear models. A sensitivity analysis for the primary outcome with the most conservative data (the worst or best outcome of that indicator in the group) will assess the robustness of the missing data at random assumption. A multiple imputation will be used to impute missing values.

The hypothesis test is two-sided; the test statistics and their corresponding *p*-values will be reported.

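### Censoring the data of patients whose allocation is broken (serious adverse events are the only trigger named) conflicts with the intention-to-treat population and with the protocol's own mid-point rule for dropouts

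*Protocol article*

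**What the plan says.** Three sections of the protocol article bear on the same patients.

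- **Blinding.** The trigger is set out first: "In the case of serious adverse events, the principal investigators at each participating center will decide whether allocation concealment needs to be broken". The consequence follows: "If allocation concealment is broken before the end of the trial, the data will be censored from analysis". Anyone affected is also given dropout status. The text gives no cut-off date and does not confine the rule to efficacy data.
- **Statistical analysis.** "The intention-to-treat analysis population, consisting of all participants who pass the randomization stage, will be the primary population", and the uses listed for it include "compliance, efficacy analysis, and safety analysis". Unblinding is not an exception. For gaps in the data, "A multiple imputation will be used to impute missing values", and a worst-or-best-outcome sensitivity analysis is planned for the primary outcome.
- **Eligibility criteria (drop-out criteria).** For dropouts, "if the time is past the mid-point of participation in the overall study, the data should be included in the efficacy statistics". One of the listed reasons for dropout is "Experienced unexpected events during treatment and are unfit to continue with the trial", which can describe a patient with an SAE.

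The Safety evaluation section lists severe adverse events among the safety outcomes and requires serious ones to be reported within 24 hours. The Abstract says that the number, nature and severity of adverse events will be recorded.

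**The concern.** An unblinded patient has already been randomised. The Statistical analysis section therefore keeps that patient, while the Blinding section takes the data out.

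The exclusion is not neutral. It is tied to a serious event after randomisation, and the arms differ in what could cause one: needle penetration with current in the electroacupuncture (EA) arm, penetration without current in the sham electroacupuncture (SEA) arm, and neither in the sham acupuncture (SAC) arm. Removals could therefore differ by arm and for reasons related to treatment.

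Safety is a stated aim of the trial. In arms of 44, where any serious events will be few, losing one or two of them changes the comparison visibly and always makes the affected arm look safer.

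**Working it through.** **1. The plan's own figure.** Inputs from the Sample size section: 35 per group before dropout, 20% dropout. 35 / (1 − 0.20) = 43.75, rounded up to 44 per group; 3 × 44 = 132. This reproduces the plan. The intention-to-treat set as defined is therefore 132. Under the Blinding rule it becomes 132 − u, where u is the number unblinded.

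**2. The three rules applied to one patient.** The patient has an SAE, the allocation is broken, and the patient also meets a listed drop-out criterion.

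| When it happens | Blinding | Eligibility criteria | Statistical analysis |
|---|---|---|---|
| Before the mid-point | Data out | Out of efficacy, by implication | In, efficacy and safety |
| After the mid-point | Data out | In efficacy | In, efficacy and safety |

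In neither row do the three agree. In the first row, deleting the Blinding sentence alone would still leave the mid-point rule against the intention-to-treat set.

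**3. Effect on the safety comparison.** The documents give no SAE rate, so the counts are assumptions. With k SAEs in an arm of 44 and u of those patients unblinded, the analysed proportion is (k − u) / (44 − u).

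| k | u | All randomised | Analysed under the rule |
|---|---|---|---|
| 1 | 1 | 1/44 = 2.3% | 0/43 = 0% |
| 2 | 0 | 2/44 = 4.5% | 2/44 = 4.5% |
| 2 | 1 | 2/44 = 4.5% | 1/43 = 2.3% |
| 2 | 2 | 2/44 = 4.5% | 0/42 = 0% |
| 3 | 3 | 3/44 = 6.8% | 0/41 = 0% |

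Exact (Clopper–Pearson) two-sided 95% limits: 2/44 gives 0.6% to 15.5%. For 0/42 the upper limit is 1 − 0.025^(1/42) = 8.4%.

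**4. Would there be any SAE at all?** For an assumed risk p per patient, the expected number is 132p and the chance of at least one is 1 − (1 − p)^132.

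- p = 1%: 1.3 expected, chance 73%
- p = 2%: 2.6 expected, chance 93%
- p = 5%: 6.6 expected, chance 99.9%

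These figures count SAEs. The number unblinded may be lower, down to zero.

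**5. Effect on the primary comparison.** Removing u of 44 patients moves the arm mean by (u/44) × D, where D is the difference in mean itch score between removed and retained patients. As an assumption, let D equal the largest difference between arms used in the Sample size section, 45.9 − 35.7 = 10.2 points. With u = 2 the shift is (2/44) × 10.2 = 0.46 points. The EA–SEA difference in that section is 40.4 − 35.7 = 4.7 points, so the shift is about a tenth of it. The direction is unknown.

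**The case against.** **Censoring might mean a cut-off at unblinding.** On that view the patient stays in the intention-to-treat set and later values are treated as missing and imputed. This is a workable plan, but it is not what the text says: it gives no cut-off, speaks of censoring from analysis, and adds dropout status. Even if it was intended, the sections would still need to be reconciled.

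**The events are not lost.** This stands. A reader might infer that the rule deletes SAEs, or that the trial would report none when some had occurred. The documents do not support that: the Safety evaluation section requires adverse events to be recorded with date, severity, duration and treatment measures, and serious ones to be reported to the principal investigators and the Ethics Committee. What the rule removes is the place of those events in the analysis by arm.

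**Few patients may be affected.** This also stands. Breaking the allocation is discretionary. The trial is single-blind and the treating physicians already know the arm, so there may be little call to break it. The number could be zero, and having both of two SAE patients unblinded is the extreme of the range shown.

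**The analysis plan may settle it.** This does not answer the point. The article does not leave the matter open; it states an exclusion that conflicts with its own analysis population. A separate plan would have to overrule one of the two.

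**Conclusion.** The Blinding rule is wrong as written. On its plain reading it is an outcome-dependent exclusion that contradicts the all-randomised population for efficacy and safety, and it also differs from the mid-point rule.

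The consequence is mainly for the safety comparison. In an arm of 44 with two SAEs, the analysed rate falls from 4.5% to 2.3% or to 0%, depending on whether one or both patients are unblinded. This rests on assumed counts and on taking the data to include safety data, which the text does not exclude.

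A reader might also infer that the efficacy result would be materially biased. The documents give no basis for that: no direction can be stated, and the illustrative shift for two removals is about half a point.

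The point should be fixed before data are seen, but it does not threaten the design or the sample size.

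**What to change.** Remove the censoring sentence from the Blinding section and align it with the Eligibility criteria and Statistical analysis sections. The aligned text should say that:

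- unblinded patients and all other dropouts, whether before or after the mid-point, stay in the intention-to-treat efficacy set and in the safety set;
- all their adverse events are counted in the arm to which they were randomised;
- breaking the allocation is recorded and reported as a protocol event;
- any exclusion of itch scores obtained after unblinding is confined to a sensitivity analysis.

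Deleting the one sentence is not enough, because the mid-point rule could still drop the same patients from the efficacy analysis. The change concerns only the use of data. When the allocation is broken and whether a patient is withdrawn are left as they are.

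The cost is a wording change in three sections and one small sensitivity analysis. No planned figure changes: the sets stay at 44 per group and 132 in total.
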